## Abstract

**Introduction:**

Smartphone and social media use is prevalent during adolescence, with high levels of use associated with lower levels of mental well-being. Secondary schools in the UK have introduced policies that restrict daytime use of smartphones and social media, but there is no evaluation on the impact of these policies on adolescent mental well-being. The SMART Schools Study aims to determine the impact of daytime restrictions of smartphone and social media use on indicators of adolescent mental well-being, anxiety, depression, physical activity, sleep, classroom behaviour, attainment and addictive social media use.

**Methods and analysis:**

This is a natural experimental observational study using mixed methods. Secondary schools within a 100 mile radius of the recruiting centre in the West Midlands (UK) have been categorised into two groups: Schools that restrict (intervention) and permit (comparator) daytime use of smartphones. We aim to recruit 30 schools (20 restrictive, 10 permissive) and 1170 pupils aged 12–13 and 14–15 years. We will collect data on mental well-being, anxiety and depressive symptoms, phone and social media use, sleep and physical activity from pupil surveys, and accelerometers. Policy implementation measures and data on individual pupil factors will be collected through school staff surveys, and website/policy analysis. Six case study schools will explore individual, school and family/home factors that influence relationships between school smartphone policies, smartphone/social media use, and mental well-being. Economic evaluation will be completed through a cost–consequence analysis from an education sector perspective.

**Ethics and dissemination:**

Ethical approval was obtained from the University of Birmingham’s Research Ethics Committee (ERN_22-0723). Parents/carers of pupil participants can complete a form to opt their child out of the study. Pupil, school staff and parent/carer participants are asked to complete online/written consent (or assent). Findings will be disseminated through policy briefings, resources for schools, social media, reports, and open access publications.

**Trial registration number:**

ISRCTN77948572.

Strengths and limitations of this studyThis is a natural experimental observational study exploring the impact of school phone policies that restrict daytime use of smartphones and social media on adolescent mental well-being and associated behaviours, and the cost implications of these policies from an education sector perspective.Pupils will self-report data on time spent on their smartphones and social media by using data from their iOS or Android apps.Pupil outcomes will be collected from an online survey that includes validated measures for mental well-being, anxiety and depressive symptoms, addictive social media use, motives for social media use, health-related quality of life and demographic data; and from accelerometers measuring physical activity and sleep.Qualitative research will explore how individual, school and family/home factors influence relationships between school phone policies, phone/media use and mental well-being.This is a cross-sectional study and is limited to data collected in England.

## Introduction

Globally, mental disorders (eg, anxiety and depression) are the leading cause of disability in adolescents (age range: 10–19).^1 2^ In the UK, one fifth (20%) of adolescents are reported to have a mental health disorder,^3^ mostly anxiety and depression.^2^ Half of all mental health disorders start before the age of 14,^4 5^ and if left untreated, mental health problems are highly likely to persist well into adulthood.^2 6^ Poor mental well-being also negatively affects other aspects of adolescents’ lives, including cognitive, social and physical behaviours.^6 7^ For example, poor mental well-being is associated with higher rates of disruptive behaviour, school absence and lower educational attainment.^8 9^ Sleep problems are also common among adolescents diagnosed with anxiety and depression, and evidence suggests a bidirectional relationship between sleep disturbances and mental health problems.^10^ Levels of physical activity also decline significantly during adolescence, and this coincides with increased onset of mental health problems.^4 11^ Hence, adolescence is a crucial period for mental health interventions,^7^ and there is a pressing need to improve and develop approaches to mental health prevention and intervention.^6^

Smartphone and social media use is prevalent during adolescence, and accounts for the majority of their overall screen time.^12 13^ In the UK, most adolescents (98%) own a smartphone, and are reported to be active users of social media (93%),^14^ with comparable trends reported in other Western populations.^15^ Samples in the USA and the UK (2021–2022) estimate that the time adolescents spend on smartphones and social media ranges between one and a half hours and eight and a half hours per day,^12–14 16 17^ with most adolescents spending between 1 and 3 hours per day.^14 16 17^ Problematic social media use is also prevalent, with 12% of adolescents in England reported to exhibit addictive use behaviours.^18^

In moderation, smartphone and social media use (eg, <2 hours per day) can be advantageous for mental well-being and mental health,^19–24^ as well as other associated health and behavioural outcomes (eg, sleep, physical activity, classroom behaviour and attainment). However, at higher levels of use, the reverse effect tends to be seen, with increasing time spent on smartphones and social media associated with decreasing levels of mental well-being and higher levels of anxiety and depression.^17 19–21 23 25 26^ Poor academic performance, disruptive classroom behaviour and less time spent in physical activity and sleep are also more likely in adolescents who spend a greater proportion of time on smartphones and/or social media.^19–23 25 26^ Reducing the time adolescents spend on smartphones and social media is thus a plausible intervention to improve mental well-being, possibly operating through improving the related behavioural outcomes (eg, physical activity, sleep, academic performance, classroom behaviour). However, uncertainties in the strength of associations between smartphone/social media and mental well-being exist, and this is mainly due to reliance on self-reported use.^15 27–29^ Furthermore, individual (eg, gender, age, socioeconomic status)^13 16 30–33^ and family/home (eg, parental usage and attitudes toward technology)^34–37^ factors are also likely to impact on relationships between smartphone/social media use and mental well-being.

There is considerable evidence that school-based interventions can have beneficial effects on adolescent mental well-being and associated behavioural outcomes (eg, sleep, physical activity, classroom behaviour and attainment).^38–41^ Whole-school environment interventions that promote lifestyles conducive to good health are reported to have a more pronounced effect on mental well-being than individual approaches targeting knowledge and beliefs.^38 42^ A whole-school approach targets physical and social influences of health, and through the alignment of school policies, values and practices with effective school leadership, the whole school approach seeks to promote a set of values, attitudes and behaviours that encourage the development and maintenance of positive physical, social, cognitive and emotional habits.^38 40^ Evidence suggests that whole school policies related to health and well-being can: (1) reduce overall screen time; (2) positively influence mental well-being; and (3) improve physical activity, sleep, educational attainment and reduce disruptive classroom behaviour.^43–45^ Therefore, whole school policies aiming to influence smartphone and social media use have the potential to positively impact on adolescents’ mental well-being.

School phone policies that restrict daytime phone/media use are an example of a current whole-school environment intervention. In the UK, Australia, Sweden, Czech Republic and elsewhere, many schools have introduced school policies that restrict daytime use of smartphones in order to reduce classroom disruptive behaviour and cyberbullying incidents and improve attainment.^44 46 47^ We suggest that these policies have the potential to lower the overall time adolescents spend on the smartphones/social media, which may improve mental well-being and associated behavioural outcomes. However, there is currently no evaluation of the effect of school smartphone policies on mental well-being and there is limited evidence on how smartphone policies are implemented in schools.^48^

The SMART Schools Study aims to determine the impact of school daytime restrictions of smartphone and social media use on adolescent mental well-being (primary outcome), anxiety, depression, physical activity, sleep, classroom behaviour, attainment and addictive social media use. We will do this by comparing impacts in two different secondary school phone policy contexts: (1) schools that do not permit smartphone use during recreational time in the school day (intervention); and (2) schools that permit smartphone use during recreational time (breaks/lunchtimes) (comparator). We will also explore how variation in school-based, individual and family/home factors influences the relationship between school phone policies, smartphone and social media use and mental well-being. We will conduct an economic evaluation in the form of a cost–consequence analysis from an education sector perspective.

## Methods and analysis

This is a natural experimental observational study using mixed methods, taking place between April 2022 and July 2024. Quantitative and qualitative data will be collected from all schools in the sample (n=30) to compare outcomes between restrictive (intervention) and permissive (comparator) school policies and to complete an economic evaluation. Qualitative data will be collected from six case study schools to understand the contextual factors that could influence relationships between school policies, smartphone and social media use and mental well-being.

### Intervention: school smartphone policies that restrict daytime use

The intervention and data capture are directed by our logic model (figure 1) which integrates multiple theories and evidence. First, we adhere to displacement theories^19^ to propose that reducing the time adolescents spend on phones/media (ie, restricting school time use) is optimal for mental well-being. Overuse can displace other mental well-being promoting activities (eg, sleep and physical activity) and very low use can deprive adolescents of interactions that support mental well-being (eg, affect and relationships).^19 21 23^ Second, psychological motives drive phone/media use; motives related to enhancement and social interactions promote mental well-being and motives related to coping and conformity (eg, Fear of Missing Out) are associated with problematic use (addiction) and poor mental well-being.^49 50^ Hence the school policy and ethos have the potential to influence adolescents’ motives for using phones/media, which may impact on mental well-being. Third, the ecological model of social influence proposes three agents that shape well-being and technology use, including the school environment, home/family and individual factors.^51^ Finally, policy enactment and implementation process models^39 52 53^ identify that school policy implementation effects will be shaped by social processes (eg, training, leadership, compliance, administration, family-–school interactions).

**Figure 1 F1:**
[figure not shown]
Logic model and theory of change for the influence of school policies that restrict daytime use of smartphones on mental well-being and other associated behavioural and health outcomes in adolescents.

Informed by our patient and public involvement (PPI) activities and school smartphone policy analysis, the components of the intervention (ie, restrictive school smartphone policies) are presented in table 1. In table 2 we have outlined variations in school smartphone policies and our classification of these variations into two school policy groups: restrictive (intervention) and permissive (comparator).

**Table 1 T1:** Components of the intervention, guided by the template for intervention description and replication (TiDieR) checklist^75^

TiDieR components	SMART Schools intervention
Description	School policy prohibiting the use of smartphones during the school day
Materials	The policy may be communicated to parents/carers and adolescents in a variety of ways, such as through school information packs, assemblies, letters and/or the school website
Procedures	Adolescents are not permitted to use their smartphones during lessons or recreational time in the school day, and their smartphones must not be seen in school during these times
Provider	Schools (or MATs*) develop their own policies, often in consultation with school staff, parents and/or school governors and in relation to the school ethos
Mode of delivery	The SLT and school staff enact the school policy and are required to administer behavioural consequences for adolescents who use their smartphone during the day, such as smartphone confiscation, detention and/or parent–school meeting
Time period	Schools vary in terms of how long their school smartphone has been implemented
Tailoring	Schools have developed policies according to their specific school contexts (or MATs*). Policies usually apply to the whole school, although in some schools sixth form pupils (age 16+) may be permitted to use their smartphones during the school day (this age group will not be investigated in this study)
Adherence and fidelity	The degree to which pupils and teachers adhere to the school policy, and parents/carers are in support of the policy varies across schools

*MATs: non-profit companies that manage more than one academy.^76^

MAT, multiacademy trusts; SLT, senior leadership team.

**Table 2 T2:** Classifications of variations in school smartphone policies as restrictive (intervention) and permissive (comparator)

Restrictive school smartphone policies (intervention)	Permissive school smartphone policies (comparator)
Allow smartphones onto school premises but insist these are not to be used during the school day and are turned off and out of sight	Allow pupils to carry smartphones and use them at any time point during the day
Allow smartphones onto school premises, but only allow use if sanctioned by teaching staff for educational activities (eg, use of calculator)	Allow pupils to carry smartphones and use them at specific time points during the day (eg, breaks and lunch)
Allow smartphones onto premises but insist they are left in a specified place during the school day for example, school reception or lockers	Allow pupils to carry smartphones and use them for personal use with consent from school staff
Pupils are not allowed to carry their smartphones onto school premises at any time	Allow pupils to carry smartphones and use within designated areas or zones

### Study setting

The sampling frame comprises UK secondary schools (ages 11–19) located within a 100 mile radius of the recruiting centre in the West Midlands. Sixty-four local authorities are included in the sampling frame from the West Midlands, East Midlands, East, South East, South West and North West. The schools are situated in regions of high and low levels of deprivation and in areas that have high^54^ and low proportions of Black, Asian and Minority Ethnic (BAME) groups.^55 56^ Schools other than state-funded mainstream schools (special schools, pupil referral units and independent schools) were excluded because it was expected that there would be additional influences on mental well-being. Schools that did not have an accessible smartphone policy and/or had different smartphone policies for the year groups 8 and 10, and schools with missing data that were required for the propensity score estimation (see sampling and participants) were also excluded (n=10,810). A total of 1345 secondary schools are included in our sampling frame; 1220 schools with policies classified as restrictive (intervention) and 125 as permissive (comparator).

### Sampling and participants

To improve the comparability of the two school groups, stratified sampling based on propensity scores was employed.^57^ We obtained routine data from the Department for Education on the following school characteristics: region, school type, urban or rural, total pupil roll size, Income Deprivation Affecting Children Index (IDACI),^58^ inclusion of a sixth form, selective or non-selective admissions policy, religious affiliation and the proportion of pupils with the following characteristics: male, from BAME groups, English as an additional language, eligible for free school meals and special education needs. Propensity scores were calculated using restrictive or permissive school smartphone policies as the outcome and school characteristics as explanatory variables. Propensity score terciles were then used to create three groups with subsequent division by restrictive or permissive policy type, resulting in six distinct sampling groups. Schools in each group have been randomly ordered and are being invited sequentially to participate, aiming to recruit six to seven schools from each restrictive tercile and three to four from each permissive tercile to achieve a sample size of 20 schools with restrictive and 10 schools with permissive policies.

In participating schools, two classes of mixed ability year 8 (age 12–13) and year 10 (age 14–15) pupils are recruited. We are focusing on adolescents in this age range because of the age of onset and prevalence of mental illness,^5^ and the prevalence of smartphone and social media use by adolescents aged 12–15.^7 14 59^ Within this age range we may also be able to observe potential differences in smartphone/social media use relationships with well-being.^33^ For example, year 8 pupils are likely to be newer users of phones/media and physical activity levels begin to decline at this age, particularly among girls.^7 13^ In year 10, pupils are more likely to be established phone/media users, mental well-being tends to be lower, and this age group are approaching the peak onset of mental health conditions.^4^ In addition to adolescent participants, the form teacher for each class recruited (or an equivalent teacher responsible for the class) and a member of senior leadership team (SLT) who is responsible for the school smartphone policy are recruited from each school.

### Sample size calculation

To account for the imbalance of schools in our sample that have permissive (n=125) and restrictive policies (n=1220), we are recruiting schools using a 2:1 (restrictive: permissive) ratio. The primary outcome of mental well-being will be measured using the Warwick-Edinburgh Mental Well-Being Scale (WEMWBS; score range=14–70).^60^ To detect a mean difference in score of three points (considered the minimum clinically important difference^60^ between the two school groups), assuming a SD of 6.8^61^ and an ICC of 0.1 (a conservative estimate^62^), with 90% power and 5% significance, we require 20 schools in the restrictive and 10 schools in the permissive smartphone policy groups, with an average cluster size of 39 (1170 pupil participants in total; 780 in the restrictive, and 390 in the permissive policy groups).

In each participating class, we aim to recruit a minimum of 19–20 pupils (67% if estimated class size n=30). In studies with multiple layers of clustering (here classes within schools), it is conservative to treat clusters within clusters as one larger cluster, which is the approach used here.^63^

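### The stated 90% power needs normal quantiles and equal-sized schools; with 30 schools and a t reference on at most 28 degrees of freedom, the same inputs give about 88%

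*Protocol article*

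**What the plan says.** The Sample size calculation section gives every input needed to rebuild the figure:

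- Target: "To detect a mean difference in score of three points" on WEMWBS, which the article treats as the minimum clinically important difference.
- Variability: "assuming a SD of 6.8" and "an ICC of 0.1 (a conservative estimate").
- Error rates and schools: "with 90% power and 5% significance, we require 20 schools in the restrictive and 10 schools in the permissive smartphone policy groups", following from "we are recruiting schools using a 2:1 (restrictive: permissive) ratio". Sidedness is not stated.
- Pupils: "with an average cluster size of 39 (1170 pupil participants in total; 780 in the restrictive, and 390 in the permissive policy groups").

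The section names no formula, no reference distribution and no allowance for variation in school size. It sets a minimum of 19–20 pupils per class of about 30, and it treats classes and schools as one level of clustering, which it calls conservative. The Analysis of pupil outcomes section plans multilevel linear models that account for repeated measures and for classes and schools. These adjust for the school-level variables used in the propensity score and for individual sociodemographic variables. That section names no test statistic or degrees-of-freedom method.

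**The concern.** Every pupil in a school shares the same policy, so the information on the policy contrast comes from 30 schools, only 10 of them permissive. Between-school variance has to be estimated from those 30 schools. A normal reference ignores the uncertainty in that estimate and overstates power. With hundreds of schools this would not matter. With 30 it costs about two points, and the stated calculation has no margin to absorb the loss.

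At stake is whether 90% power and 5% significance hold together for the stated inputs. Planned power and the three-point target are likely to be cited if the WEMWBS comparison is not significant, so the figure should be one that the stated design delivers.

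**Working it through.** **Inputs**, all from the Sample size calculation section: difference 3; SD 6.8 (variance 46.24); ICC 0.1; 20 and 10 schools; 39 pupils per school, so 780 and 390 pupils; two-sided 5% (an assumption about sidedness, which reproduces the plan's figure).

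**Step 1: reproduce the plan's figure.**

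- Design effect, equal schools: 1 + (39 − 1) × 0.1 = 4.8.
- Pupils needed in the smaller group under independence, normal quantiles, 2:1 ratio: 1.5 × (6.8 × (1.960 + 1.282) / 3)² = 81.0.
- Inflated: 81.0 × 4.8 ≈ 389 pupils; 389 / 39 = 9.97, so 10 schools, and 20 in the other group.
- SE = √(46.24 × 4.8 × (1/780 + 1/390)) = 0.924; 3 / 0.924 = 3.247.
- Power = Φ(3.247 − 1.960) = 90.1%.

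The plan's figure reproduces. At 38 pupils per school the same formula gives 89.96%, so 39 is the smallest school size that reaches 90%.

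**Step 2: use a t reference with school-level degrees of freedom.**

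- Degrees of freedom, unadjusted: 30 − 2 = 28. Critical value: 2.048 instead of 1.960.
- Power from the noncentral t distribution, 28 degrees of freedom, noncentrality 3.247: **88.0%**.
- Noncentrality needed for 90%: 3.359. Detectable difference: 3.359 × 0.924 = **3.10 points**.
- If 1.96 is kept, the two-sided tail area of t on 28 degrees of freedom is 6.0%, not 5%.

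For scale, 90% under this reference would take about 60 pupils in each of the 30 schools (90.0%), or 21 + 11 schools of 39 (90.5%).

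**Step 3: unequal school sizes, as a sensitivity check.** The documents give no coefficient of variation (CV) of school size, so these values are assumed. The planned multilevel model weights schools according to their information. Its relative efficiency is approximately 1 − CV² × L × (1 − L), with L = 3.9 / 4.8 = 0.8125, so L(1 − L) = 0.152. The noncentrality is 3.247 × √(relative efficiency).

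| Assumed CV | Relative efficiency | Power, t on 28 df |
|---|---|---|
| 0 | 1 | 88.0% |
| 0.2 | 0.994 | 87.8% |
| 0.3 | 0.986 | 87.5% |
| 0.4 | 0.976 | 87.2% |

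**Step 4: features of the analysis that the calculation does not use** (all values assumed; t on 28 df, equal schools, unless stated).

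- Averaging two WEMWBS measures, pupil-level correlation 0.6 to 0.9: 89.1% down to 88.3%.
- Covariates explaining 10% of between-school variance: 90.5%.
- ICC 0.09 instead of 0.1: 90.4%.
- In the other direction, school-level covariates use degrees of freedom. At 15 degrees of freedom with no variance explained, power is 85.8%; at 15 with 10% explained, 88.6%; at 15 with 20% explained, 91.2%.

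**The case against.** The strongest reply is that nothing is miscalculated. The standard design-effect formula returns the plan's own figures, and the only shortfall that needs no invented input is about two points of power. That is small beside the uncertainty in the ICC: 0.09 in place of 0.1 restores 90%, and the article calls its ICC conservative. The article also specifies no t test, and the choice of degrees of freedom may sit in an analysis plan that is not shown.

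Most of this stands, and it is why the point is minor. It does not rescue the stated figure. The power statement is made in this document, for these inputs. Whichever test is chosen later, 30 schools with these inputs do not give 90% power at a true 5% level. The offsets are not claimed in the sample size section, and they do not all run one way. The Sampling and participants section lists 13 school characteristics in the propensity score, and the Study setting section names six regions. Adjusting for all of them takes at least 12 + 5 = 17 school-level parameters, so 28 degrees of freedom is the most favourable count.

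A reader might also infer that any variation in school size pushes power down to about 86%. The documents do not support this, for three reasons:

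- No CV of school size is given, so any such figure is a scenario.
- A figure of 85.7% arises at an assumed CV of 0.3 from the design effect 1 + ((1 + CV²) × 39 − 1) × 0.1. That formula suits an analysis that does not weight schools efficiently. With the planned multilevel model the result at that CV is 87.5%, and about 86% needs a CV near 0.6.
- The class minimum limits the variation. If every school had two classes meeting a minimum of 19 and holding at most 30, sizes would lie between 38 and 60. With a mean of 39 the CV could not exceed √((39 − 38) × (60 − 39)) / 39 = 0.12. Power would then be 87.6% even by the less favourable formula.

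**Conclusion.** The point holds, as a minor one. For the stated inputs, power is about 88% at a true 5% level, not 90%; equivalently, the difference detectable with 90% power is about 3.1 points, not 3.0. This rests on a two-sided test, equal schools of 39, 28 school-level degrees of freedom and no covariate adjustment. Unequal sizes lower it by less than one point over assumed CVs up to 0.4 under the planned type of model. Repeated measures and covariate adjustment may move it either way.

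It would be wrong to conclude that the sample size is in error or that the study is materially underpowered. The stated figure follows correctly from a common approximation. What it lacks is a small-sample allowance and any margin to absorb one.

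**What to change.** In the sample size section, restate the power as about 88%, saying that it uses a t reference with school-level degrees of freedom, equal school sizes and no covariate adjustment. Alternatively, keep 90% power and give the detectable difference as 3.1 points.

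If unequal school size is mentioned, show it as a labelled sensitivity range based on the efficiency of the planned multilevel model: about 87.8%, 87.5% and 87.2% at assumed CVs of 0.2, 0.3 and 0.4. Add a sentence that repeated measures and covariate adjustment may raise or lower the figure.

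The cost is one restated figure, slightly less favourable than before, and a sentence or two of text. The design and recruitment targets stay as they are; no extra schools or pupils are needed.
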